### Sample Size Calculation

The sample size was calculated using G*Power (version 3.1.9.7; Heinrich Heine University Düsseldorf). On the basis of a related study [32], an effect size of 0.953 was determined, derived from the difference in the 6MWD between the experimental group (mean 35.89, SD 8.46 laps) and the control group (mean 26.76, SD 10.57 laps) after the intervention. The significance level (α) was set at .05, and the power (1 – β) was set at 0.95. The calculation indicated that 30 participants were required for each group. To account for a potential 10% loss to follow-up, 34 participants per group were planned for recruitment, resulting in a total sample size of 68 participants.

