**Methods:**

A total of 68 participants will be recruited and allocated to 2 groups matched in age and gender, with consideration given to the preferences of participants and their guardians. The control group will receive standard in-hospital medical treatment and health education, whereas the experimental group will receive a 6-month digital therapy–based aerobic exercise intervention in addition to standard care. Outcomes will be assessed at baseline and 3 and 6 months, with data collected for analysis. The primary outcomes are the 6-minute walk distance and the timed scores (in seconds) for the timed up and go and stair climb tests. The secondary outcomes include body composition, grip strength, and quality of life measured using the Pediatric Quality of Life Inventory version 4.0.

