### Statistical Analysis

Data will be analyzed using SPSS (version 26.0; IBM Corp). Primary models using the intention-to-treat principle will be conducted for all primary and secondary outcomes. Data normality will be assessed initially. Nonnormally distributed data will be presented as medians with IQRs. Between-group comparisons (intervention vs control) for these variables will be conducted using the Mann-Whitney *U* test. Within-group comparisons (baseline vs each follow-up) will be conducted using the Wilcoxon signed rank test. Categorical data will be reported as numbers with percentages and analyzed using the chi-square test. Differences in primary and secondary outcomes between the intervention and control groups across all assessment time points will be evaluated using mixed-model analysis. Statistical significance will be defined as a *P* value of <.05, with multiple comparisons adjusted using the Bonferroni method.

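### The sample size spends the full .05 on 6-minute walk distance alone, while the analysis has three primary outcomes and a Bonferroni rule with no defined family; if the three share alpha, power is about 0.89, not 0.95

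*Protocol article*

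**What the plan says.** The abstract (Methods) lists the primary endpoints: "The primary outcomes are the 6-minute walk distance and the timed scores (in seconds) for the timed up and go and stair climb tests". In the body, all three tests again sit under the Primary Outcome Measure heading, and each is assessed at baseline, 3 months and 6 months.

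Statistical Analysis plans mixed models comparing the groups on every primary and secondary outcome over all assessments. It sets significance at P < .05, "with multiple comparisons adjusted using the Bonferroni method". It does not say which comparisons the adjustment covers.

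Sample Size Calculation uses one outcome. It reports that "an effect size of 0.953 was determined" from the walk-test results of a related study: experimental mean 35.89 (SD 8.46) laps, and "the control group (mean 26.76, SD 10.57 laps) after the intervention". It continues: "The significance level (α) was set at .05", and power "was set at 0.95". The result: "The calculation indicated that 30 participants were required for each group". A 10% allowance for loss raises this to 34 per group, 68 in total. The section mentions neither the other two primary outcomes nor the Bonferroni rule.

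**The concern.** Three stated elements have to fit together: the number of primary outcomes, the multiplicity rule, and the alpha used for sizing. Here the sizing gives the whole .05 to one test, while the analysis section says alpha will be divided in some way.

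Two different things may be at stake, depending on what the Bonferroni clause means. If it divides alpha among tests that include the walk-distance group comparison, the stated power is too high for the test that will be performed. If it does not, the stated power stands, but three primary outcomes are each tested at .05 with nothing protecting the overall error rate. These are alternatives; they do not occur together.

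The open family also leaves room to decide after the data are seen which threshold applies and which outcome carries the claim.

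**Working it through.** **Inputs** (Sample Size Calculation, unless noted): means 35.89 and 26.76; SDs 8.46 and 10.57; d = 0.953; alpha .05; power 0.95; 30 per group; 10% loss. Number of primary outcomes: 3 (abstract and Primary Outcome Measure). Sidedness is not stated. I assume two-sided, because one-sided .05 gives 25 per group and only two-sided .05 gives 30.

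**Step 1: reproduce the plan's figures.**

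- Pooled SD = √[(8.46² + 10.57²)/2] = 9.573. d = (35.89 − 26.76)/9.573 = 9.13/9.573 = 0.954, which agrees with the stated 0.953 apart from the last digit.
- Two-sample t test by the noncentral t distribution, with n per group: df = 2n − 2, noncentrality = d√(n/2).
- n = 30: df = 58, noncentrality = 0.953 × √15 = 3.691, critical t at two-sided .05 = 2.002, power = 0.9525. With n = 29, power is 0.946. The smallest adequate n is therefore 30, as stated.
- 30/0.9 = 33.3, rounded up to 34 per group, 68 in total. This also reproduces.

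So the full .05 was spent on the single walk-distance comparison.

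**Step 2: the same test with alpha divided among m tests.** Only the critical value changes.

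| Tests in family (m) | Alpha per test | Critical t, n = 30 | Power, n = 30 | Power, n = 34 (no loss) |
|---|---|---|---|---|
| 1 | .05 | 2.002 | 0.952 | 0.972 |
| 2 | .025 | 2.301 | 0.914 | 0.947 |
| 3 | .0167 | 2.465 | 0.886 | 0.926 |
| 6 | .0083 | 2.732 | 0.827 | 0.882 |

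m = 3 is one test per primary outcome. m = 2 could be the two follow-up comparisons within walk distance. m = 6 puts all three outcomes at both follow-up visits into one family. Every family of two or more is below 0.95, even with no loss to follow-up. At m = 3 the type II error is 1 − 0.886 = 0.114, against the planned 0.05.

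Power of 0.95 at .05/3 would need 38 evaluable per group (37 gives 0.948, 38 gives 0.953). After 10% loss that is 38/0.9 = 42.2, so 43 per group and 86 in total, against 34 and 68.

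**Step 3: the other branch, no division across outcomes.** Three tests at two-sided .05 with all nulls true: if independent, family-wise error = 1 − 0.95³ = 0.143. By simulation of three equally correlated normal statistics it is 0.125 at correlation 0.5 and 0.109 at 0.7. The article gives no correlations, so these are assumptions.

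**Step 4: the other two primary outcomes.** No effect size is given for timed up and go or stair climb, so their power cannot be computed.

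**The case against.** The strongest reply is that the Bonferroni family is not defined. The clause comes right after the sentence on mixed models over the assessment times, so it may concern only contrasts over time within a model, and then walk distance keeps its 0.95. That stands. The threshold .05/3 is the natural reading of three primary outcomes, not something the document states. A reader might infer that the design simply lacks its stated power; the document does not support so flat a claim. Nor does it support treating .05/6 as the likely threshold, since a mixed model could yield one test per outcome.

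A reader might also infer that the sample size was miscalculated. It was not: every figure reproduces.

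It can be added that naming the family is often left to an analysis plan. But the sizing alpha, the three primary outcomes and the Bonferroni rule are all stated in the article. The point is that they do not fit together, not that a detail is absent.

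Two further replies depend on things the article does not state.

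- **A success rule.** If any one of three sufficed, and all had d = 0.953, the chance of at least one success at .05/3 would be about 0.97 to 0.999 (correlation 0.7 to 0, normal approximation). If all three were required, no alpha split would be needed, but the relevant power would be joint: 0.9525³ = 0.86 if independent with the same d.
- **Baseline adjustment.** A baseline correlation of about 0.45 would bring power at .05/3 back to about 0.95. No correlation is given, and the sizing claims no such gain.

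Finally, 0.89 is respectable, and even 0.83 exceeds the common 0.80 benchmark. The Limitations section calls the study preliminary. That bears on severity.

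**Conclusion.** The point holds as one of consistency and multiplicity, of moderate severity. The sizing is computed correctly but for a test that the analysis section may not perform.

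On the natural reading, with alpha shared by the three primary outcomes, walk-distance power is about 0.89 rather than 0.95. If Bonferroni leaves that comparison untouched, the three primary tests are not protected at 5%. With no success rule stated, no reading of the Bonferroni clause gives both 0.95 power for walk distance and 5% control over the three primary outcomes.

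This rests on the plan's own d = 0.953, a two-sided t test, equal groups, and no gain from baseline adjustment. On those assumptions the trial is not grossly underpowered for walk distance. Nothing can be said about power for the other two outcomes.

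**What to change.** Choose one of two wordings, preferably before recruitment opens and in any case before outcome data are analysed by group.

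1. **One primary outcome.** Name walk distance at one stated visit as the single primary outcome, tested at two-sided .05. Make timed up and go and stair climb key secondary outcomes, tested afterwards in fixed order or by Holm. The visit must be chosen explicitly, because the sizing refers only to the post-intervention result of the related study and is not tied to 3 or 6 months. The existing calculation then stands.
2. **Three primary outcomes.** State that Bonferroni covers exactly those three tests, one per outcome at a stated visit. Restate walk-distance power as about 0.89 with 30 evaluable per group, and say that the other two outcomes have no power assumption.

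In either case, state that the test is two-sided. Neither option needs more patients. The cost is that two outcomes lose primary status under the first, or that the published power is less favourable under the second. Keeping both three primary outcomes and 0.95 power for walk distance would require 86 children instead of 68.

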### Quality Control and Quality Assurance

All researchers involved in this study possess appropriate clinical research qualifications. Before the commencement of the clinical trial, the project leader or principal investigator conducted comprehensive training sessions for the research team. Personnel responsible for evaluations were specifically trained in evaluation procedures and operational methods, with their competency regularly assessed. Quality control measures include monthly monitoring and evaluation by inspectors within each group, as well as quarterly monitoring and evaluation by the study team’s inspectors. To ensure the integrity of the study, a data and safety monitoring committee was established to oversee the quality of each process. The clinical research unit is responsible for maintaining the quality and safety of the study, ensuring both the safety of participants and the validity of the data. The trial may be terminated if the intervention is found to be ineffective or if significant safety concerns arise based on the assessment of data quality, efficacy outcomes, and AEs. In the event of an AE, the principal investigator will evaluate the situation and determine whether to suspend the intervention.

### Ethical Considerations

#### Ethics and Informed Consent

This study has been approved by the Medical Ethics Committee of Xinhua Hospital, affiliated to Shanghai Jiao Tong University School of Medicine (XHEC-C-2023-062), and all study participants will provide written informed consent.

#### Dissemination and Publication Policy

Study results will be published in peer-reviewed journals and presented at conferences and relevant stakeholder engagement activities. There will be no information that can identify participants in any publication. Participants who explicitly express a wish to be informed about the research outcome will be contacted and offered to receive an article or poster with a lay summary of the study.

## Results

Recruitment will be conducted from December 2025 to September 2026. It is expected that the intervention group will show significantly greater improvements in physical function, physical activity levels, and fatigue management compared to the control group and that the effectiveness of digital therapy for rehabilitation training after radiotherapy and chemotherapy for neuroblastoma in children can be demonstrated. The findings of this study are anticipated to be published by late 2026 or early 2027.

## Discussion

### Expected Findings

DTx represent an innovative treatment modality that facilitates real-time remote guidance and intervention quality monitoring. This approach reduces the need for frequent hospital visits while enhancing the efficiency of interventions [29]. Aerobic exercise has been widely recognized for its significant role during and after oncology treatment, contributing to improvements in physical fitness, muscle strength, and functional capacity. Additionally, it alleviates symptoms such as pain and diarrhea, shortens hospitalization duration, and promotes mental health and emotional well-being [33]. It should be pointed out that the primary goal of this “aerobic digital intervention” program is not to directly maximize cardiorespiratory endurance (such as maximal oxygen consumption) in the traditional sense but to provide a safe, feasible, and tolerable home physical activity initiation program for participants with different levels of fatigue to improve physical function, physical activity level, and fatigue management.

The integration of aerobic exercise interventions with DTx has shown promise in enhancing intervention efficacy through personalized, multilevel management of exercise programs. To the best of the authors’ knowledge, this study is the first controlled trial to evaluate the impact of an aerobic exercise intervention combined with digital therapy on motor performance in children with neuroblastoma.

The primary objective of this study is to establish a digital management intervention protocol for children with neuroblastoma by comparing the effectiveness of DTx combined with an aerobic exercise intervention against traditional in-hospital visits and health promotion strategies. The study outcomes are expected to demonstrate significant improvements in cardiopulmonary fitness, muscle strength, body composition, and quality of life. These findings will provide an evidence-based rationale for the future implementation of digital therapy–supported aerobic exercise programs in this population.

### Limitations

Despite its potential, this study has several limitations that should be considered when interpreting the results. First, the single-center design and small sample size restrict the generalizability of the findings. Future research should involve multiple centers across different regions and include larger samples to enhance external validity. Second, although outcome assessors and statisticians were blinded, participants and care providers were not. Furthermore, for participants with a preexisting preference, allocation was based on that preference rather than randomization. This nonrandomized allocation for a subset of participants introduces potential performance and expectation biases. As a preliminary investigation, this study provides foundational insights that can inform the design of a more rigorous randomized controlled trial in the future. Finally, the digital therapy platform and exercise programs are self-developed, and no formal large-scale usability testing was conducted before the intervention. While the design was informed by pediatric expertise and in-study engagement metrics supported feasibility, future iterations would benefit from structured usability testing to optimize the platform before broader implementation.

### Conclusions

This study represents an important first step in aerobic digital therapy for pediatric neuroblastoma. It provides evidence that rehabilitation after chemoradiotherapy in pediatric patients with neuroblastoma can improve physical function, physical activity levels, and fatigue management. In the future, expanding to multiple centers to conduct targeted surveys of different types of childhood cancers will help validate the effectiveness of digital therapy–based aerobic exercise.

## Abbreviations

6MWD: 6-minute walk distance
AE: adverse event
DTx: digital therapeutics
HR: heart rate
PedsQL 4.0: Pediatric Quality of Life Inventory version 4.0
SCT: stair climb test
TUG: timed up and go
